### Lifestyle intervention

All participants will register for the GetHealthy NSW program. All women will receive individually-tailored telephone-based lifestyle coaching for 3 months, consisting of up to 13 telephone calls from an exercise physiologist with nutrition training, exploring healthy eating, physical activity, and weight management. Lifestyle coaching is provided by Remedy Healthcare under the GethealthyNSW[19] program, which has been offered to all NSW residents for free by the NSW government since 2009. Medical referral is not required. Information given to participants is consistent with national guidelines on physical activity and nutrition, which are also recommended by national PCOS guidelines[3].

# Study Assessments

## Study Assessments

### Study Procedures

Participants will attend for two clinic visits, Baseline/Pre-intervention and Post-intervention.

During these visits they will complete the majority of the outcome measures for the trial.

In addition, the following outcomes are also collected outside of the two clinic visits:

- Credibility of the treatment, expectations, and perceived treatment allocation are collected immediately after the first acupuncture treatment
- Reproductive: Menstrual cyclicity from menstrual diaries
- Participants will complete an exit survey about the acceptability of the study procedures
- Participants will wear an accelerometer for 5-7 days in the week before attending for the baseline visit, and in Week 11
- Participants and treating acupuncturists will collect data on adverse events throughout the study

#### Pre-intervention/ Baseline visit

The purpose of the baseline visit is to obtain informed consent, collect baseline and demographic measures, randomise the participant, and organise the acupuncture treatments for the participant.

*Informed consent*

If the research assistant is not a practising acupuncturist, the participant will be telephoned by [name], an acupuncturist and researcher, in order to provide details about the acupuncture treatment and answer any queries about acupuncture. This is essential so that the participant can provide informed consent after understanding the risks and benefits of acupuncture treatment. This telephone call will take place prior to the baseline clinic visit.

During the clinic visit, which will take place at the National Institute of Complementary medicine, Campbelltown Campus, Western Sydney University, the participant will meet with the research assistant to provide informed consent.

*Baseline and demographic/medical measures*

The participant will have baseline outcome measures taken as per the following section on Data Collection. Briefly they include:

- Anthropometric measures and blood pressure
- Surveys on quality of life, anxiety and depression, weight self-efficacy, and internal locus of control.
- Measures of insulin resistance by blood tests collected by Laverty Pathology
- Testosterone, Free testosterone and Free Androgen Index collected by Laverty Pathology
- Clinical Hyperandrogenism as assessed by the Ferriman Gallwey score
- Heart rate using ECG monitoring at Headbox laboratory on the WSU Campbelltown Campus and also using a hand-held ambulatory monitor at the same time

Participants will also provide demographic and medical history details.

*Randomisation*

Participants will be assigned a randomisation ID number.

*Acupuncture treatments*

Participants are provided with information about the acupuncture treatments, will choose a treating acupuncturist for the intervention, and the research assistant will organise the participants’ acupuncture treatments according to the schedule.

#### Credibility, expectancy and perceived treatment allocation

Immediately following the first treatment, participants will complete the Credibility and Expectancy Questionnaire and question on perceived treatment allocation. This can be done online at the acupuncturist’s clinic or via email, or on paper and returned to the research assistant by fax or email.

#### Post-intervention visit

At the post-intervention visit which takes place after the participant has completed all her acupuncture treatments, the participant completes the same outcome measures as at the baselinepre-intervention visit but without the demographic/medical questionnaire.

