#### Dealing with missed sessions

At the time of enrolment, participants are to be made aware of the nature of their commitment over the twelve week treatment period and encouraged to notify the research office, [name] or the treating practitioner as soon as a break in treatment is foreseen. If treatments are missed, all attempts will be made to complete ten treatments within the eight weeks, providing there is at least a 2 day interval between treatments A break in the intervention schedule may be unavoidable, due to illness or holiday. If the acupuncturist becomes aware that a break of more than two weeks is likely, they will be instructed to liaise with [name] for advice on how to deal with this. [name] or the research assistant will liaise with the participant to determine the cause of missed sessions and will attempt as much as possible to implement appropriate measures to minimise further breaks in between treatments.

As analysis will be by intention-to-treat (that is, all data will be analysed even if a participant has dropped out from the trial), a minimum number of treatment sessions to meet the protocol has not been specified.

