### Practitioner background

A minimum of six practitioners have been chosen to administer the treatments. They are have a Bachelor degree in Chinese Medicine, have five or more years of clinical experience and are registered with the Chinese Medicine Registration Board.

Practitioners will receive training from [name], an experienced acupuncture researcher. Training will take place 4-6 weeks prior to anticipated start of recruitment. They will receive a detailed Practitioner Training Manual. Training will be “hands on”. Refresher training will be provided if there has been a break of two months or more in between administering the trial interventions to participants.

Participants are free to choose which practitioner they wish to see according to convenience (location, availability etc) however they are to be aware that there may be a “waitlist” for particular practitioners. Practitioners may also notify the research assistant or [name] when they are unable to take on new participants temporarily due to other commitments.

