#### Other outcomes

- Physical activity levels will be quantified using accelerometers which will be worn by participants in the week before attending for the baseline visit, and in Week 11 (minutes per week of light, moderate and vigorous activity; number of steps per day; number of sedentary hours per day).
- Data on compliance with the lifestyle coaching program and change in dietary habits will be provided by Gethealthy NSW at baseline and 3 months.
- Participants will record the dates of their menstrual cycle using a menses calendar.
- Participants and treating acupuncturists will be provided with Adverse Events forms on which to record adverse events.

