# Data Collection

Data on recruitment, retention, adherence and acceptability rates will be entered into Redcap clinical trial management software. These are defined as:

1. Recruitment rates (number of enquiries and number of enrolments per month of active recruitment; percentage conversion to enrolment measured as n enrolled/n of enquiries, and n enrolled/n potentially eligible);
2. Retention rate (n completing 12 week intervention and outcome measures/n enrolled)
3. Adherence rates (n completing at least 8 of 11 acupuncture treatments and 4 of 6 Neurova treatments; n of hours of wear of the Neurova^TM^ device/percentage of women who wore the device for the prescribed 96 hr duration; n completing all recommended phone calls with the GHS);
4. Acceptability is measured using an exit survey which includes questions on perceived benefits of body acupuncture, AEA, and health coaching, perceived detriments of being in the trial, likelihood of recommending the study to family or friends measured on a 5 point Likert scale ranging from “I would definitely participate/recommend it” to “I would definitely not participate/recommend it”;

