## Measures of insulin resistance

Participants will attend for a 2 hr Oral Glucose Tolerance Test and Insulin test prior to attending for the baseline visit and at the 3-month follow-up. Insulin will be calculated using the Area Under the Curve (AUC) method. Participants will attend for these tests at accredited pathology collection centres (Laverty Pathology).

Biomarkers that are related to insulin resistance and PCOS are collected at the same time and include Sex Hormone Binding Globulin, total and free testosterone.

Abnormal results will be followed up by phone and letter to the participant and GP by [name], who is a practising GP. Participants will be asked to attend their GP for follow-up. If participants are diagnosed with diabetes, they are excluded from the trial.

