## Proposed Analyses

Recruitment, retention and adherence rates are presented with descriptive statistics. Mixed model ANOVAs will be used to determine within-group differences for continuous outcomes between baseline and 3 months, and ANCOVAs for between-group differences for continuous outcomes with baseline score as a co-variate. Intention-to-treat analysis will be used.

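### The post-intervention visit is timed by completion of acupuncture in one place and by week 12 elsewhere, and the retention endpoint mixes treatment completion with outcome availability

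*Protocol*

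**What the plan says.** **Timing of the final visit.** Section 7.1.1 (Post-intervention visit) reads "At the post-intervention visit which takes place after the participant has completed all her acupuncture treatments". It gives no week and no window.

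Other places use the calendar and make no distinction between arms:
- Appendix 1 has one column for Visit 2, at week 12.
- Section 8.2 schedules the glucose tolerance and insulin tests "prior to attending for the baseline visit and at the 3-month follow-up".
- Section 9.2 analyses "within-group differences for continuous outcomes between baseline and 3 months".
- Section 7.1.1 (Other outcomes) has accelerometers "worn by participants in the week before attending for the baseline visit, and in Week 11".

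**Interruptions and stopping.** Sections 6.1.3 and 6.2.3 foresee interruptions ("If the acupuncturist becomes aware that a break of more than two weeks is likely") and set no minimum number of sessions, because "As analysis will be by intention-to-treat (that is, all data will be analysed even if a participant has dropped out from the trial"). Sections 6.1.5 and 6.2 (Practitioner background) tell women that "they are to be aware that there may be a “waitlist” for particular practitioners". Section 5.5.2 asks a woman who withdraws whether she will still attend the final visit or complete the final surveys, and keeps her data unless she objects.

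**Retention.** Section 8, item 2 defines it as "Retention rate (n completing 12 week intervention and outcome measures/n enrolled"). Item 3 of the same list defines adherence separately, with thresholds of 8 of 11 body acupuncture treatments and 4 of 6 Neurova treatments. Sections 2.1.1 and 2.2.1 make retention a primary endpoint.

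**The concern.** Two rules for one visit will be applied differently by different staff. The treatment-based rule has no meaning in the lifestyle-alone arm, which has no acupuncture to complete. It also fails for a woman who attends, say, 8 of 11 sessions and never withdraws: she is adherent under Section 8, yet never reaches the trigger in Section 7.1.1. If the rule is followed, time from baseline to final measurement can depend on arm. An ANCOVA adjusted for baseline score does not correct that.

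Retention raises a separate difficulty. The study exists to inform a fully powered trial, and for planning that trial the useful quantity is the share of randomised women who supply outcomes. The definition as worded does not isolate it. Treatment completion enters both retention and adherence, and outcome availability is never reported alone.

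**Working it through.** **1. The protocol's own figure.** Sections 4.1 and 9.1 randomise 39 (13 per arm) to analyse 30, allowing 20-25% attrition.
- 30/(1 - 0.20) = 37.5, so 38; 30/(1 - 0.25) = 40. The stated 39 lies between them.
- Implied attrition: (39 - 30)/39 = 9/39 = 23.1%, inside the stated range.

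The sample size reproduces, and nothing below changes it.

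**2. When treatment ends if sessions run to schedule.**
- Body acupuncture (Section 6.1.3): 2 x 2 + 4 + 3 = 11 sessions over 2 + 4 + 3 x 2 = 12 weeks. The last session falls at about week 12, so there is no slack.
- AEA (Section 6.2.3): the listed frequency gives 2 x 2 + 4 = 8 sessions over 2 + 4 x 2 = 10 weeks, but the stated total is 6. On the listed frequency there are about 2 weeks of slack.
- Lifestyle alone: no sessions, so only the calendar rule can apply.

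**3. Visit week if Section 7.1.1 is followed and a break is not made up.** Break lengths are assumptions. The visit is taken at the later of week 12 and the end of treatment.

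| Break | Body acupuncture | AEA (listed frequency) | Lifestyle alone |
|---|---|---|---|
| 0 weeks | 12 | 12 (sessions end at 10) | 12 |
| 2 weeks | 14 | 12 | 12 |
| 4 weeks | 16 | 14 | 12 |

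**4. Effect on the weight comparison.** Shift in an arm's mean = (share of women who slip) x (weeks of slip) x (weekly weight change after week 12). The protocol gives none of the three.

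**5. Retention under the two definitions.** Enrolment and randomisation happen at the same visit (Section 5.2), so the denominator is 39 either way. Suppose 30 women complete everything and k of the other 9 stop treatment but give outcomes (k is an assumption). As defined, retention is 30/39 for any k. Based on outcomes alone it is (30 + k)/39, shown with Wilson 95% intervals:

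| k | As defined | Outcomes alone |
|---|---|---|
| 0 | 76.9% (61.7-87.4) | 76.9% (61.7-87.4) |
| 3 | 76.9% | 84.6% (70.3-92.8) |
| 6 | 76.9% | 92.3% (79.7-97.3) |
| 9 | 76.9% | 100% (91.0-100) |

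The understatement ranges from 0 to 23.1 points. Within an arm of 13, each such woman is worth 1/13 = 7.7 points: 10/13 = 76.9%, 11/13 = 84.6%, 12/13 = 92.3%.

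**The case against.** The strongest reply is that the protocol fixes the assessment by calendar in several places, and that one descriptive clause in Section 7.1.1 agrees with them whenever sessions run on time. That is right as far as it goes. A reader might infer that follow-up will slip in the acupuncture arms alone. The documents do not establish this: slippage follows only if the clause is applied over the schedule, and on the listed AEA frequency a break of up to about two weeks need not pass week 12. The make-up rule also tries to compress sessions rather than extend treatment. However, its figures (ten sessions in eight weeks) fit neither regimen, so it is no assurance. No delay length is attached to the practitioner waitlists.

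A reader might also infer that women who stop treatment are lost to the analysis, so that outcomes come mainly from completers. Section 5.5.2 and the intention-to-treat statement say otherwise for women who withdraw. The remaining gap is the woman who misses sessions without withdrawing.

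A large weight bias is another tempting inference. At an assumed 0.2-0.3 kg per week and 2-4 weeks of slip, the shift is 0.4-1.2 kg, or 25-76% of the 1.58 kg that Section 1.1 cites as the lowest effect. That needs every woman in the arm to slip. If 3 of 13 do, it is 0.09-0.28 kg, or 6-18%. It also assumes weight keeps falling after the 3 months of coaching end. These are illustrations, not estimates.

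On retention, the 12-week wording may mean the period rather than every session. The control arm also has an intervention to complete (up to 13 calls), so no direction of bias between arms is shown. Outcome availability could still be counted at reporting. These points stand, but they leave a primary endpoint with two possible meanings.

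**Conclusion.** The point holds as a contradiction about visit timing and as a poorly fixed endpoint definition. Section 7.1.1 conflicts with Appendix 1, Section 8.2 and Section 9.2, has no meaning for controls, and leaves non-withdrawing women who miss sessions without a visit time. If followed, it puts a body acupuncture visit at about week 14 after a two-week break that is not made up, against week 12 for controls. The consequence for the weight difference cannot be sized from the protocol.

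Read literally, retention falls 7.7 points in an arm for each woman who stops treatment but gives outcomes. The overall gap is 7.7 points (76.9% against 84.6%) if 3 of the 9 planned non-completers do so. That number is an assumption, and the gap is zero if none do.

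Severity is moderate. The sample size stands, the primary results are descriptive, and weight is secondary. The retention count can be repaired from the data afterwards; a visit held at the wrong time cannot.

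**What to change.** 1. In Section 7.1.1, set Visit 2 (weight, blood tests, heart rate variability, surveys) at week 12 from randomisation, with one window for all three arms (for example +/-1 week). It applies whether treatment is complete, interrupted or stopped, and make-up sessions do not move it. Use the same timepoint wording in Sections 8.2 and 9.2 and Appendix 1.
2. In Section 8, define retention as the number with week-12 outcome measures divided by the number randomised, reported by arm and overall.
3. Report treatment completion under adherence only.

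The cost is amendment wording. The downside is that a few women will be measured before a late make-up session.

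The session counts bear on when treatment ends and must be reconciled by the sponsor: the AEA total of 6 against a frequency giving 8, the synopsis total of 12 against 11 in Section 6.1.3, and the make-up figures in Sections 6.1.3 and 6.2.3. No view is taken here on which is right.

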#### Other outcomes

- Physical activity levels will be quantified using accelerometers which will be worn by participants in the week before attending for the baseline visit, and in Week 11 (minutes per week of light, moderate and vigorous activity; number of steps per day; number of sedentary hours per day).
- Data on compliance with the lifestyle coaching program and change in dietary habits will be provided by Gethealthy NSW at baseline and 3 months.
- Participants will record the dates of their menstrual cycle using a menses calendar.
- Participants and treating acupuncturists will be provided with Adverse Events forms on which to record adverse events.

# Data Collection

Data on recruitment, retention, adherence and acceptability rates will be entered into Redcap clinical trial management software. These are defined as:

1. Recruitment rates (number of enquiries and number of enrolments per month of active recruitment; percentage conversion to enrolment measured as n enrolled/n of enquiries, and n enrolled/n potentially eligible);
2. Retention rate (n completing 12 week intervention and outcome measures/n enrolled)
3. Adherence rates (n completing at least 8 of 11 acupuncture treatments and 4 of 6 Neurova treatments; n of hours of wear of the Neurova^TM^ device/percentage of women who wore the device for the prescribed 96 hr duration; n completing all recommended phone calls with the GHS);
4. Acceptability is measured using an exit survey which includes questions on perceived benefits of body acupuncture, AEA, and health coaching, perceived detriments of being in the trial, likelihood of recommending the study to family or friends measured on a 5 point Likert scale ranging from “I would definitely participate/recommend it” to “I would definitely not participate/recommend it”;

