## Endpoints

### Primary Endpoint

Recruitment, retention and adherence rates; credibility; acceptability; and safety over the recruitment and intervention periods.

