### Treatment regimen

#### Treatment frequency and duration

Women allocated to the acupuncture group will receive a total of 11 treatments of acupuncture over 12 weeks (twice a week for the first two weeks, weekly for four weeks, then fortnightly for 3 treatments). This tapering schedule is consistent with usual clinical practice. Needles are retained for 30 minutes.

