### Treatment regimen

#### Treatment frequency and duration

Women allocated to the AEA group will receive a total of 6 treatments of acupuncture over 12 weeks (twice a week for the first two weeks, then fortnightly for four treatments).

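### Coaching adherence is an all-or-none count over a tailored number of calls, while needling adherence allows about a quarter to a third of sessions to be missed

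*Protocol*

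**What the plan says.** Section 2.2.1 (Primary Endpoint) lists "Recruitment, retention and adherence rates; credibility; acceptability; and safety over the recruitment and intervention periods".

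Section 8 (Data Collection), item 3, defines adherence. For needling it is "n completing at least 8 of 11 acupuncture treatments and 4 of 6 Neurova treatments". For coaching it is "n completing all recommended phone calls with the GHS" (GHS is read here as the GetHealthy NSW service). The same item gives two measures of AEA device wear: hours worn, and the percentage of women who wore it for the full 96 hours.

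The needling denominators come from the two treatment-regimen sections: "Women allocated to the acupuncture group will receive a total of 11 treatments of acupuncture over 12 weeks" and "Women allocated to the AEA group will receive a total of 6 treatments of acupuncture over 12 weeks".

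Section 6.4.1 (Lifestyle intervention) states "All women will receive individually-tailored telephone-based lifestyle coaching for 3 months, consisting of up to 13 telephone calls". Section 6.3 makes coaching the whole of the control intervention. Section 9.2 (Proposed Analyses) says that adherence rates are presented descriptively. The two Other outcomes sections (under 7.1.1 and at the end of section 8) say that GetHealthy NSW will supply coaching compliance data at baseline and 3 months, but they define no further coaching measure.

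**The concern.** Three features of the coaching measure make it a weak readout.

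- **Unequal bar.** Needling tolerates 3 missed sessions of 11, or 2 of 6. Coaching tolerates no missed call. The protocol gives no reason for the difference.
- **Moving denominator.** The number of calls is tailored up to a ceiling of 13. A woman who takes 12 of 13 recommended calls is non-adherent, while one who completes a much shorter course is adherent. The measure can therefore rank women opposite to the amount of coaching they received.
- **No graded companion.** Device wear also has an all-or-none criterion, but it is paired with hours of wear. Coaching has nothing equivalent.

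Coaching is the background treatment in all three arms, and this is the only adherence figure that section 8 gives for the lifestyle-alone arm. The study exists to inform a larger trial. A low coaching figure that comes mainly from the cut-off could be misread as poor uptake of that background treatment.

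**Working it through.** **Inputs from the protocol.** Cut-offs are 8 of 11, 4 of 6 and all recommended calls (section 8). Calls number at most 13 (section 6.4.1). There are 13 women per arm (section 4.1).

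**Assumptions.** The protocol gives neither an attendance rate nor the usual number of recommended calls. I apply the same attendance p per contact to sessions and calls, and take 4 to 13 recommended calls.

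**Step 1: the cut-offs as proportions.** 8/11 = 72.7%; 4/6 = 66.7%; coaching = 100%.

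**Step 2: independent contacts.** P(adherent to needling) is the binomial tail P(X ≥ r | n, p). P(all m calls) = p^m.

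| p | ≥8 of 11 | ≥4 of 6 | 13/13 calls | 10/10 | 6/6 | 4/4 |
|---|---|---|---|---|---|---|
| 0.80 | 83.9% | 90.1% | 5.5% | 10.7% | 26.2% | 41.0% |
| 0.90 | 98.1% | 98.4% | 25.4% | 34.9% | 53.1% | 65.6% |
| 0.95 | 99.8% | 99.8% | 51.3% | 59.9% | 73.5% | 81.5% |

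To reach the 83.9% in the first row, per-call attendance would have to be 0.839^(1/6) = 0.971 for 6 calls, or 0.839^(1/13) = 0.987 for 13 calls.

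In an arm of 13 at p = 0.80, the expected number adherent is 13 × 0.839 = 10.9 (body acupuncture) or 13 × 0.901 = 11.7 (AEA). For coaching it is 13 × 0.055 = 0.7 (13 calls) to 13 × 0.262 = 3.4 (6 calls).

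**Step 3: attendance clustered within women.** Let p vary between women as Beta(4,1), which has mean 4/5 = 0.80.

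- All m calls: E(p^m) = 4/(4+m). For 13 calls this is 4/17 = 23.5%; for 6 calls it is 4/10 = 40.0%.
- k of n contacts: P(X = k) = 4(k+1)(k+2)(k+3) / [(n+1)(n+2)(n+3)(n+4)].
- ≥8 of 11: 4 × (990 + 1320 + 1716 + 2184) / 32760 = 24840/32760 = 75.8%.
- ≥4 of 6: 4 × (210 + 336 + 504) / 5040 = 4200/5040 = 83.3%.

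The gap narrows but remains.

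**Step 4: a proportionate coaching cut-off.** Two-thirds of recommended calls means 4 of 6, or 9 of 13 (13 × 2/3 = 8.67, rounded up; 9/13 = 69%).

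- Independent, p = 0.80: 90.1% (4 of 6) and 90.1% (9 of 13).
- Beta(4,1): 83.3% (4 of 6). For 9 of 13 it is 4 × (1320 + 1716 + 2184 + 2730 + 3360) / 57120 = 45240/57120 = 79.2%.

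Both are close to the needling figures. A 70% cut-off would not match: with whole calls it requires 5 of 6 (83%) or 10 of 13 (77%), which is stricter than 4 of 6.

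**Step 5: sensitivity to the session totals.** The protocol is not consistent here. The synopsis gives 12 acupuncture treatments against 11 in section 6.1.3. The AEA schedule in section 6.2.3 adds to 4 + 4 = 8 against its stated total of 6. These passages must be reconciled. With the other denominators the needling cut-offs would be 8/12 = 67% and 4/8 = 50%, so the distance to 100% would be no smaller.

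**The case against.** The strongest defence is that completing an individually tailored course as recommended is a reasonable meaning of adherence. The criterion is visible in its own label, adherence is only described, no comparison of coaching with needling is planned, and no progression threshold is attached. Section 8 also uses an all-or-none criterion for 96-hour device wear, so full completion is not demanded of coaching alone. All of this stands, and it limits the harm. It does not supply the graded measure that device wear has and coaching lacks.

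A reader might infer three stronger things that the protocol does not support.

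- *That the measure cannot show whether coaching uptake differs between arms.* The same rule applies in all three arms, so the proportion can be tabulated and compared by arm. It is coarse, not unusable. The GetHealthy NSW compliance data may also hold more detail.
- *That the control arm will show low adherence.* This depends on an attendance rate and a number of calls that the protocol does not give. Thirteen calls is the ceiling, and independence exaggerates the gap, because a woman who disengages tends to miss several contacts. The 5.5% is the lower end of the range shown for p = 0.80.
- *That the full trial would be redesigned on an artefact.* No planned decision rests on this figure, so that is conjecture.

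The section 6.1.3 and 6.2.3 statements that no minimum number of sessions is specified concern inclusion in the intention-to-treat analysis. They do not remove the section 8 cut-offs.

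**Conclusion.** The point holds as a cheap improvement to a primary feasibility measure. The unequal cut-offs (73% and 67% against 100%) and the dependence on the number of recommended calls follow from the protocol's text alone. The size of the distortion rests on the assumption of equal attendance for calls and sessions. At mean attendance 0.80, the share meeting 8 of 11 exceeds the share completing every call by about 58 to 78 percentage points if contacts are independent (83.9 − 26.2 for 6 calls; 83.9 − 5.5 for 13). Under Beta(4,1) clustering the gap is about 36 to 52 points (75.8 − 40.0; 75.8 − 23.5). The direction is the same for every attendance level and call count tabulated. The consequence is a less informative and possibly misleading description of coaching uptake, chiefly in the lifestyle-alone arm. No hypothesis test is affected.

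**What to change.** In section 8, item 3, define coaching adherence as the number of calls completed, the number recommended, and their ratio for each woman, summarised by arm. Keep the proportion completing all recommended calls as a supplementary figure.

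If a cut-off is wanted, use at least two-thirds of recommended calls (4 of 6, 9 of 13). This equals the AEA cut-off and lies slightly below 8 of 11. Rounding to whole calls still makes it uneven for short courses (4 of 5 is 80%), so the counts should remain the main measure.

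The change is to a reporting definition only; the coaching itself is untouched. The cost is a wording amendment, plus confirmation that the compliance data from GetHealthy NSW include calls completed and calls recommended for each woman. The protocol does not say that they do.
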